### Cardiac biomarkers

Blood will be taken in gel serum tubes, and the serum will be banked and analysed at the Core Biochemical Assay Laboratory, Cambridge. Hs-CRP and N-terminal pro brain natriuretic peptide (NT-proBNP) will be measured by immunoassays on the Siemens Dimension EXL autoanalyser. All reagents and calibrators are supplied by Siemens, and assays will be performed according to the manufacturer’s instructions.

IL-6 will be measured in duplicate using ultrasensitive electrochemical luminescence immunoassay on the Mesoscale Discovery assay platform and read on the MesoScale Diagnostics Sector Imager 6000. All reagents and calibrators will be supplied by MesoScale Discovery.

### Stopping criteria

Dose-escalation stopping criteria will be met if two patients within a trial group experience any combination of: a SAE defined as possibly, probably or definitely related to the trial drug (ie, it is a SAR), an adverse event that is severe and at least possibly related to the trial drug or any of the objective stopping criteria detailed box 1. The following will then occur:Box 1Objective stopping criteria triggering a Data Monitoring Committee safety review of dose escalationQTcB >500 ms (or >530 ms if baseline QTcB=450–480 ms) OR QTcB change from baseline >60 ms (based on an average of triplicate electrocardiogram (ECGs)).Acute pulmonary oedema or congestive heart failure.Symptomatic systolic BP <90 mm Hg and/or diastolic blood pressure (BP) <60 mm Hg OR persistent symptomatic systolic BP 80–90 mm Hg for >15 mins OR severe hypertension (as defined by BP >180/120 mm Hg).ST-elevation myocardial infarction (STEMI) occurrenceAtrial fibrillation with rapid ventricular response >150/min, supraventricular tachycardia or bradycardia that requires treatment or is recurrent or persistent.Sustained ventricular tachycardia or ventricular fibrillation.Any patient who develops doubling of creatinine.Systemic hypersensitivity reaction that cannot be attributed to an identifiable cause.If a life-threatening infection is confirmed clinically with a positive microbiological test.Signs suggestive of hepatic failure including encephalopathy, increasing ascites, signs of coagulopathy, liver pain and/or tenderness on palpation, hypoglycaemia presumed to be secondary to liver failure and active GI bleeding. Withdrawal also if alanine aminotransferase (ALT)>3 ULN.Seizure activity, coma, severe lethargy or somnolence.Risk of respiratory insufficiency requiring intubation.

Dosing will be immediately discontinued for the patients experiencing the event.Dosing will be halted for all other patients currently in the treatment period of the trial (ie, patients receiving treatment in the same group).A safety review by the independent DMC will be conducted to determine how to proceed with the trial.Any further single instances of the events outlined above for the same group will trigger a further DMC safety review.Any patients who have their dosing discontinued will be withdrawn from the trial.

Additionally, specific objective stopping criteria are set out in box 1, which may trigger an unscheduled DMC review prior to any further dose escalations. Specific and general withdrawal criteria are also listed in online supplementary file 1.

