**Figure 1 F1:**
[figure not shown]
Trial design per patient. Each patient will make a total of eight study visits. IL-2, interleukin; V, visit.

There are two follow-up visits (V7 and V8). Assessments during both visits will include a medical review, physical examination, vitals, ECGs and safety bloods tests. Additionally, at V8, a follow-up thyroid function blood test and echocardiogram will be performed.

In addition, during visits V2 and V7 (figure 1), cardiac biomarkers (high sensitivity C reactive protein (hs-CRP), IL-6, brain-type natriuretic peptide (BNP) and troponin) and lymphocyte subsets (including Treg level, see below) analysis will be performed. During visit V8, cardiac biomarkers will be reaassessed.

A total of 25 patients, five in each of the five dosing groups, will be included in part A (drug:placebo ratio of 3:2). In line with current phase I trial designs, a sentinel dosing approach will be employed whereby the first two patients of each group will be allocated to either aldesleukin or placebo in a random order. After a blinded safety review of these first two patients, the remaining patients will then be dosed (see figure 2).

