#### Part B

Patients admitted with a primary diagnosis of non-ST elevation myocardial infarction will be recruited from the medical and cardiology wards at Cambridge University Hospitals NHS Foundation Trust. Patients may continue to receive trial treatments if they are transferred to the local interventional centre at Royal Papworth Hospital. Participants will be given at least 24 hours to review the patient information sheet prior to formal consent. Dosing should commence within 8 days of screening. All visits and blinding procedures will be the same as part A. However, in part B, a total of 32 patients will be recruited, eight patients in each of the four dosing groups (drug:placebo ratio of 6:2). A sentinel approach to dosing will also be employed in each group. After a blinded safety review of the first two patients, the remaining cohort will be randomly allocated to study treatments as shown in figure 3. The visit schedule for each patient is the same as part A (figure 1).

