### Dose-escalation strategy

The first group of patients in part A will receive 0.3×10^6^ IU of aldesleukin daily. Thereafter, a blinded review of patient data by the blinded Trial Management Group (TMG) including review of AEs, blood results, ECGs, clinical records and, where possible, drug pharmacodynamics and pharmacokinetics. The TMG will be composed of an experienced, accredited early phase lead physician (LILACS chief investigator), a research physician/scientist, a research nurse, trial coordinator and an unblinded study statistician (for the purposes of data analysis). All data presented by the unblinded statistician to the TMG will be in an aggregated format to preserve the blind for the other TMG members. This is consistent with the commercial standard for such early phase trials in industry. The dose in the second group will be determined after this review, and the same process will be followed in each of the following groups. The maximum dose increments allowed by the protocol between groups will be double the previous dose and capped to a maximum 3.0×10^6^ IU.

A robust set of specific and general withdrawal criteria, as well as objective stopping criteria have been put into place to maintain the safety:risk benefit, in particular due to the risk of capillary leak syndrome.

Following completion of part A, an unblinded independent Data Monitoring Committee (DMC) will review all available safety data, together with any other analyses that the committee may request. The DMC will be composed of an independent group of clinical researchers with suitable experience in experimental medicine and early phase clinical trials. These researchers are independent from the trial team and have not been involved in the setup or running of this clinical trial. They will determine whether it is safe to progress to part B, based on available safety and pharmacodynamic data provided by the unblinded statistician. After this analysis, the dose in each group will be determined based on the review of ongoing patient data by the TMG, as in part A previously. The protocol mandates that the maximum dose used in part B will not exceed that of part A. DMC will be governed by a charter set up a priori and signed up by all members prior to the commencement of the trial (see supplementary file 2).

10.1136/bmjopen-2018-022452.supp1Supplementary file 1

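### A first related SAE in a dose group has no stated compulsory route to an unblinded DMC review, and it is unclear whether a single Box 1 event has one

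*Protocol article*

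**What the plan says.** The Protocol article, under Stopping criteria, sets a count: "Dose-escalation stopping criteria will be met if two patients within a trial group experience any combination of" three kinds of event. These are an SAE at least possibly related to the drug, a severe adverse event at least possibly related to it, and any criterion in Box 1. Once the count is reached, dosing stops for the affected patients, is halted for others under treatment in the same group, and the independent DMC reviews safety. After that, "Any further single instances of the events outlined above for the same group will trigger a further DMC safety review".

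Two other pieces of text bear on single events. The heading of Box 1 describes its list as "stopping criteria triggering a Data Monitoring Committee safety review of dose" escalation, and gives no number of patients. The closing sentence of the section says of the Box 1 criteria, "which may trigger an unscheduled DMC review prior to any further dose escalations". It does not mention SAEs.

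Other checks exist. In part A (Study protocol), "After a blinded safety review of these first two patients, the remaining patients will then be dosed"; part B has the same step. Under Dose-escalation strategy, the blinded TMG reviews adverse events, blood results, ECGs and clinical records before each new dose, and "All data presented by the unblinded statistician to the TMG will be in an aggregated format". Under Safety monitoring committees, the TMG also assesses safety, blinded, at regular intervals. The one scheduled unblinded DMC review falls between parts A and B.

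**The concern.** The rule counts patients within a group, and the groups are small: three on drug in each part A group and six in each part B group. With so few treated patients, the commonest way for a harmful dose to show itself is through one affected patient, and that is the case for which the article requires no unblinded look.

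The setting makes this matter. The article states that IL-2 is currently contraindicated in both conditions studied. Its summary of low-dose experience reports no SAEs in two diabetes studies (24 and 40 patients) and one lupus study (38 patients). A related SAE among three treated heart patients would be a new signal. Two of every five part A patients receive placebo, so allocation bears directly on whether the next dose should be raised, and those who choose that dose do not know it.

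The Box 1 wording adds a practical difficulty: two readers could disagree on whether one STEMI or one sustained ventricular tachycardia has to go to the DMC.

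**Working it through.** **1. What each provision requires while only one patient in the group is affected**

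- Two-patient rule: not met.
- Further-single-instance clause: not active, because it follows from the rule having been met.
- Closing sentence on Box 1: a DMC review is possible but not required, and SAEs as such are not covered.
- Box 1 heading: suggests a review, but states no count and belongs to a box introduced inside the two-patient rule.
- Sentinel and TMG reviews: take place, blinded.
- Scheduled unblinded review: only after part A is complete.

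So a related SAE outside Box 1 has no stated compulsory route to the DMC, and a single Box 1 event has an uncertain one.

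**2. How far the dose can move first**

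The start is 0.3 MIU, each step may at most double, and the cap is 3.0 MIU (Dose-escalation strategy). The steepest permitted path over five groups is 0.3, 0.6, 1.2, 2.4, 3.0 MIU, and 3.0/0.3 = 10.

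**3. How often one group meets the rule**

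The article gives no operating characteristics, so there is no figure to reproduce. Group sizes come from the Study protocol section: "five in each of the five dosing groups, will be included in part A (drug:placebo ratio of 3:2" and "eight patients in each of the four dosing groups (drug:placebo ratio of 6:2". The event risk on drug, *a*, is an assumption.

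Drug events only, P(X ≥ 2):

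| *a* | Part A, X ~ Bin(3, *a*) | Part B, X ~ Bin(6, *a*) |
|---|---|---|
| 10% | 2.8% | 11.4% |
| 20% | 10.4% | 34.5% |
| 30% | 21.6% | 58.0% |

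The rule counts any patient in the group, so placebo events contribute. Adding two placebo patients at an assumed 5% raises the part A figures to 5.4%, 14.3% and 26.0%.

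Share of part A groups with any treated event that have exactly one, P(X = 1)/P(X ≥ 1):

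- 10%: 0.243/0.271 = 90%
- 20%: 0.384/0.488 = 79%
- 30%: 0.441/0.657 = 67%

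Over all five part A groups at constant risk, 1 − (1 − P)^5 gives at least one firing in 13%, 42% or 70% of trials (24%, 54% or 78% with 5% placebo events). The rule is therefore not inert over the whole of part A. Its weakness lies within a group, at the point where the next dose is chosen.

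**4. How often a one-event trigger would call the DMC**

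Patients on drug: 5 × 3 = 15 in part A and 4 × 6 = 24 in part B, 39 in all. As a reference risk, take the one-sided 95% upper limit for no SAEs in 24 + 40 + 38 = 102 patients: u = 1 − 0.05^(1/102) = 2.9%. This treats all 102 as dosed.

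1 − (1 − risk)^n, the chance of at least one related SAE on drug:

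| Risk | Part A (15) | Part B (24) | Trial (39) |
|---|---|---|---|
| 1% | 14% | 21% | 32% |
| 2.9% | 36% | 51% | 68% |
| 5% | 54% | 71% | 86% |

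The expected number at 2.9% is 39 × 0.0289 = 1.1. If 1% of the 18 placebo patients also have an SAE judged related, the whole-trial figure at 2.9% becomes 73%. These figures count a related life-threatening Box 1 event as a related SAE.

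**The case against.** Four objections carry weight.

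*The text does not contradict itself.* A reader might infer that the Box 1 heading makes one event sufficient and that the closing sentence then denies it. The documents do not support that. The heading gives no count, the box sits inside the two-patient rule, and the closing sentence is presented as an addition. Two patients compulsory, fewer than two discretionary, is a coherent reading. What remains is an ambiguity.

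*A single event is not invisible.* A reader might also infer that nobody looks at it, or that the TMG sees only pooled data. Aggregation applies to what the unblinded statistician presents. The TMG reviews individual adverse events, ECGs and records, does so on an ongoing basis, and must review before every dose step. Only the allocation is hidden. The tenfold rise is the permitted maximum, not a plan.

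*The detail may be elsewhere.* Supplementary file 1 holds the withdrawal criteria and risk mitigation, and the DMC charter defines the committee's function. Either may contain a single-event rule, so it cannot be said that the trial lacks one. But the article does not leave its stopping rule to those files. It sets out the count, the events and the consequences, and that rule can be judged as written.

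*Two patients is a legitimate threshold.* As a trigger for halting a group, it is a defensible balance between false alarms and sensitivity, and nothing in the article forbids it. That argues for keeping it for the halt. It does not settle who should see the first related SAE before the dose is raised.

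**Conclusion.** The point stands in a limited form. As the Stopping criteria section is written, unblinded DMC review is compulsory only after two patients in the same group have a qualifying event. A first related SAE has no stated compulsory route to the DMC, and the position of a single Box 1 event is ambiguous. Blinded reviews mitigate this but cannot tell drug from placebo.

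The size depends on assumed risks. At 10% to 30% on drug, three treated patients meet the rule in about 3% to 22% of part A groups, and between two thirds and nine tenths of groups with a treated event have only one. These figures illustrate the rule; they do not predict event rates in this trial.

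This is a worthwhile, inexpensive improvement to patient protection. It does not show that the two-patient halt is wrong or that the unseen charter is deficient.

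**What to change.** In the Stopping criteria section, state that either of the following will trigger an expedited unblinded DMC review before any further dose escalation:

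- one SAE judged at least possibly related to the drug;
- one at least possibly related life-threatening Box 1 event (STEMI, sustained ventricular tachycardia or ventricular fibrillation, or respiratory insufficiency requiring intubation).

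Keep the two-patient, within-group count for the full dosing halt. For the remaining Box 1 events, make the box heading and the closing sentence agree on whether a single event may or must go to the DMC. If the charter or supplementary file 1 is already stricter, bring this section into line with it.

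The cost is a wording amendment and use of the existing committee: about one extra expedited review per trial at the 2.9% risk, with at least one in 32%, 68% or 86% of trials at 1%, 2.9% or 5%. Escalation may be briefly delayed. The review should be tied to escalation only. An automatic bar on dosing new patients in the current group is not needed, and in part B it could cost patients their 8-day window for starting treatment.

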	Exclusion criteria	Current presentation with cardiogenic shock (systolic blood pressure <80 mm Hg, unresponsive to fluids or necessitating catecholamines), severe congestive heart failure and/or pulmonary oedema. Known active bleeding or bleeding diatheses. Known active infection requiring antibiotic treatment. Severe haematological abnormalities (haematocrit <30% and platelet cell count of <100 × 10^3^/μL and white cell count <4 × 10^3^/μL). Known malignancies requiring active treatment or follow-up (however, patients with current/a history of localised basal or squamous cell skin cancer are not excluded from participation in this trial). Known heart failure with impaired LV function (LV EF<45%). Hypotension (systolic BP <100 mm Hg, DBP <50 mm Hg) at screening. Uncontrolled hypertension (>160/100 mm Hg) at screening. History of recurrent syncope (electrocardiographic history suggestive of arrhythmia syncope (eg, bifascicular block, sinus bradycardia <40 beats per minute in absence of sinoatrial block or medications, pre-excited QRS complex, abnormal QT interval, ST segment elevation leads V1 through V3 (Brugada syndrome), negative T wave in right precordial leads and epsilon wave (arrhythmogenic right ventricular dysplasia/cardiomyopathy)). Known hepatic failure or abnormal LFTs at baseline (ALT >2 × ULN). Elevated total bilirubin levels, (TBL >1.5 × ULN) and alkaline phosphatase, ALP (ALP >1.5 × ULN), at baseline. Acute kidney injury or chronic kidney disease at stage >3B (eGFR <45 mL/min/1.73 m^2^). Respiratory failure. Known hyperthyroidism or hypothyroidism. History of drug-induced Stevens Johnson syndrome, drug reaction with eosinophilia and systemic symptoms (DRESS syndrome) or toxic epidermal necrolysis. History of recurrent epileptic seizures in the previous 4 years; repetitive or difficult to control seizures, coma or toxic psychosis lasting >48 hours. If known diabetic, uncontrolled diabetes defined as HbA1c >64 mmol/mol. Average corrected QT interval >450 ms using Bazett’s formula using triplicate ECGs (or >480 ms if bundle branch block). Known chronic active hepatitis (B or C). Known HIV infection. Current infection possibly related to recent or ongoing immunosuppressive treatment. Known autoimmune disease requiring active immunosuppressive therapy. History of organ transplantation. Any oral or intravenous immunosuppressive treatment including prednisolone, hydrocortisone or disease-modifying drugs such as azathioprine, interferon-alpha, cyclophosphamide or mycophenolate. (Other immunosuppressive therapies should be discussed with PI. Inhaled or topical steroids are permissible). Known pregnancy at screening or visit 2 (where applicable). Ongoing lactation. Inability to comply with trial procedures. Current participation in other interventional clinical trials. Contra indication to interleukin (IL)-2 treatment or hypersensitivity to IL-2 or to any of its excipients. Unwillingness or inability to provide written informed consent for participation. Any medical history or clinically relevant abnormality that is deemed by the principal investigator/delegate and/or medical monitor to make the patient ineligible for inclusion because of a safety concern.

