	Exclusion criteria	ST elevation myocardial infarction (heart attack) on this admission. Current presentation with cardiogenic shock (systolic blood pressure <80 mm Hg, unresponsive to fluids, or necessitating catecholamines), electrical instability, severe congestive heart failure and/or pulmonary oedema. Known active bleeding or bleeding diatheses. Known active infection requiring antibiotic treatment. Severe haematological abnormalities (haematocrit <30% and platelet cell count of <100 × 10^3^/μL and white cell count <4 × 10^3^/μL). Known malignancies requiring active treatment or follow-up (however, patients with current/a history of localised basal or squamous cell skin cancer are not excluded from participation in this trial). Known heart failure with impaired LV function with LV EF <35%. Hypotension (systolic BP <100 mm Hg, DBP <50 mm Hg). Uncontrolled hypertension (>160/100 mm Hg) at screening. History of recurrent syncope (electrocardiographic history suggestive of arrhythmia syncope (eg, bifascicular block, sinus bradycardia <40 beats per minute in absence of sinoatrial block or medications, pre-excited QRS complex, abnormal QT interval, ST segment elevation leads V1 through V3 (Brugada syndrome), negative T wave in right precordial leads and epsilon wave (arrhythmogenic right ventricular dysplasia/cardiomyopathy)). Known hepatic failure or abnormal LFTs at baseline (ALT >2 × ULN). Elevated TBL (TBL >1.5 × ULN) and ALP (ALP >1.5 × ULN), at baseline. Renal impairment at screening (creatinine clearance (Cockcroft-Gault) <45 mL/min). Acute respiratory failure. Known hyperthyroidism or hypothyroidism. History of drug-induced Stevens Johnson syndrome, DRESS syndrome or toxic epidermal necrolysis or contrast allergy (requiring steroid treatment). History of recurrent epileptic seizures in the previous 4 years, repetitive or difficult to control seizures, coma or toxic psychosis lasting >48 hours. Average corrected QT interval >450 ms using Bazett’s formula using triplicate ECGs (or >480 ms if bundle branch block). Known chronic active hepatitis (B or C). Known HIV infection. Current infection possibly related to recent or ongoing immunosuppressive treatment. Known autoimmune disease requiring active immunosuppressive therapy. History of organ transplantation. Any oral or intravenous immunosuppressive treatment including prednisolone, hydrocortisone or disease-modifying drugs such as azathioprine, interferon-alpha, cyclophosphamide or mycophenolate. (Other immunosuppressive therapies should be discussed with PI. Inhaled or topical steroids are permissible.) Known pregnancy at screening. Ongoing lactation. Inability to comply with trial procedures. Current participation in the active dosing phase of other interventional clinical trials. Contra indication or hypersensitivity to IL-2 treatment or to any of its excipients. Unwillingness or inability to provide written informed consent for participation. Any medical history or clinically relevant abnormality that is deemed by the principal investigator/delegate and/or medical monitor to make the patient ineligible for inclusion because of a safety concern.

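### Diastolic pressure of 50–59 mm Hg is eligible under Table 1 but lies below the diastolic stopping figure in Box 1, and Box 1 does not say whether symptoms are required or whether an unchanged entry value counts

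*Protocol article*

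**What the plan says.** **Entry limits.** In Table 1 the part A exclusion reads "Hypotension (systolic BP <100 mm Hg, DBP <50 mm Hg) at screening". The part B exclusion uses the same figures, "Hypotension (systolic BP <100 mm Hg, DBP <50 mm Hg", without naming a time point.

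**Stopping limit.** In Stopping criteria, Box 1, the first limb of the blood pressure item is "Symptomatic systolic BP <90 mm Hg and/or diastolic blood pressure (BP) <60 mm Hg". Further limbs cover persistent symptomatic low systolic pressure and severe hypertension.

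**Halt rule.** "Dose-escalation stopping criteria will be met if two patients within a trial group experience any combination of" three kinds of event: a drug-related serious adverse event, a severe adverse event at least possibly related to the drug, "or any of the objective stopping criteria detailed box 1". Relatedness is a condition of the first two kinds but not of the Box 1 items.

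**Consequences.** Patients with the event stop dosing and are withdrawn. For the rest of the group, "Dosing will be halted for all other patients currently in the treatment period of the trial". The independent DMC then decides how to proceed, and each further single event in that group prompts another review. The closing paragraph of the section adds that Box 1 lists criteria "which may trigger an unscheduled DMC review prior to any further dose escalations", without giving a patient count.

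**The concern.** A stopping limit is normally set beyond the entry limit, so that reaching it implies a change since enrolment. The systolic figures follow that order. The diastolic figures reverse it, and the blood pressure item does nothing to allow for the starting value.

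The rule may then be unable to tell new hypotension from a value the patient brought to the trial. Because no attribution is asked for, placebo patients count too. Part A groups have five patients, three of them on drug, so a halt with two withdrawals could cost much of the data at that dose level and interrupt a five-day course in the others. Box 1 is also presented as objective, so staff should not reach different answers on the same patient by parsing the sentence differently.

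**Working it through.** **1. Thresholds side by side (both parts)**

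| Pressure | Eligible at entry | Box 1, first limb | Eligible values below the Box 1 figure |
|---|---|---|---|
| Systolic | 100 mm Hg or more | below 90 mm Hg | none (10 mm Hg gap) |
| Diastolic | 50 mm Hg or more | below 60 mm Hg | 50–59 mm Hg |

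This takes each Table 1 figure as excluding on its own. If the comma there means that both must be low, the diastolic overlap is wider.

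**2. Does anything in Box 1 remove the overlap?**

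- Baseline: the QTcB item raises its limit from 500 to 530 ms when baseline QTcB is 450–480 ms. The blood pressure item has no such allowance.
- Attribution: none is required for Box 1 items.
- Persistence: a duration of more than 15 minutes is attached to one of the systolic limbs, not to the diastolic figure.
- Opportunity: vitals are taken before dosing and at 30 and 60 minutes on five dosing days, so 3 × 5 = 15 scheduled readings per patient.

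**3. The two readings of *symptomatic***

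- *Systolic only.* A well patient who enters at 55 mm Hg and stays there meets Box 1, even before the first dose. Two such patients in a group meet the halt rule.
- *Both pressures.* The same patient without symptoms is not an event, so entry status alone triggers nothing. A patient who enters at 55 mm Hg, stays there and develops symptoms put down to low pressure could still be counted, although diastolic pressure has not fallen.

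**4. Illustration, systolic-only reading**

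The documents state no false-trigger probability, so there is none to reproduce. Inputs from the documents: "A total of 25 patients, five in each of the five dosing groups" in part A; eight patients in each of four groups in part B; two patients needed per group. Check: 5 × 5 + 4 × 8 = 57, the stated total.

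Assumed input: *p*, the share of patients whose diastolic pressure is below 60 mm Hg without any drug effect. Patients are taken as independent.

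For a group of *n*: P(at least 2) = 1 − (1 − p)^n − n·p·(1 − p)^(n−1). Over all groups: 1 − (1 − a)^5 (1 − b)^4, where *a* and *b* are the part A and part B group probabilities.

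At p = 5%:
- a = 1 − 0.95^5 − 5 × 0.05 × 0.95^4 = 1 − 0.77378 − 0.20363 = 2.3%
- b = 1 − 0.95^8 − 8 × 0.05 × 0.95^7 = 1 − 0.66342 − 0.27933 = 5.7%
- all nine groups: 1 − (1 − a)^5 (1 − b)^4 = 29.5%

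| Assumed p | Part A group (n = 5) | Part B group (n = 8) | At least one of nine groups |
|---|---|---|---|
| 1% | 0.1% | 0.3% | 1.6% |
| 5% | 2.3% | 5.7% | 29.5% |
| 10% | 8.1% | 18.7% | 71.4% |
| 20% | 26.3% | 49.7% | 98.6% |

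The last column runs from negligible to near certain according to an input the documents do not supply. It shows that the ambiguity could matter, not how often a false halt would occur.

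**The case against.** The strongest reply is grammatical. Within the blood pressure item, capital OR separates the limbs, while a lower-case and/or joins systolic to diastolic inside one limb that opens with *symptomatic*. Read that way, the limb means symptomatic hypotension on either component. This is a fair reading, and it removes the automatic trigger. It is not the only one: *symptomatic* stands directly before systolic, and the next limb repeats the word together with systolic.

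A reader might therefore infer that patients with a diastolic value of 50–59 mm Hg enter already past the stopping limit and will halt the trial with no drug effect. The documents do not support that as a flat statement. It fails if the word covers both pressures. On either reading a halt needs two patients in the same group; a single Box 1 event may at most prompt a DMC review. The rule also speaks of patients experiencing a criterion, which suggests something that happens on trial, although that is not spelled out.

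Other points that stand:
- A halt is a pause pending review, not the end of dosing for unaffected patients. The DMC is described as reviewing unblinded data and pre-dose vitals are recorded, so it could recognise an entry value.
- A sensitive trigger without attribution is a defensible choice where the drug is contraindicated and capillary leak is the named risk.
- Symptomatic low pressure ordinarily means symptoms of low pressure, not any symptom at all. An investigator may also exclude a patient on safety grounds.
- Low readings after dosing cannot simply be called spurious, since most patients are on drug (3:2 and 6:2). That is why *p* above is restricted to values without drug effect.
- The full protocol and supplementary file 1, which holds the withdrawal criteria, are not shown and may settle the wording.

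None of this removes the mismatch between two figures that the article prints in full.

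**Conclusion.** The concern holds in a conditional form. What is certain is a 10 mm Hg band of diastolic pressure, 50–59 mm Hg, that is eligible in both parts and lies below the Box 1 figure, in a halt rule with no baseline or attribution condition for that item. The systolic limits do not have this problem, and the QTcB item shows that baseline was allowed for elsewhere in the same box.

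What follows from it depends on one word. On the systolic-only reading, two well patients with unchanged pressure in one group are enough for a halt. On the reading that covers both pressures, the remaining weakness is smaller: symptoms can complete the criterion without a fall in diastolic pressure.

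The false-halt probabilities are illustrative only. They require the systolic-only reading, an assumed prevalence and independence between patients, and they should not be quoted as an estimate for this trial. The case for correction rests on the printed thresholds.

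**What to change.** In Box 1, state whether *symptomatic* governs the diastolic limb, and state whether a diastolic value unchanged from baseline counts as an event; the QTcB item already offers a pattern for handling baseline. Then reconcile the Box 1 blood pressure item with the part A and part B hypotension exclusions in Table 1. Which figure to keep or change is a clinical decision for the sponsor's clinicians, and this review proposes none. If the full protocol or supplementary file 1 already settles the wording, carry that wording into Box 1.

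The cost is one line by amendment, with no extra patients, visits or measurements, since pre-dose vitals are already recorded.
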